| **Outcome measures and time points:**  The outcomes are QoL as measured by mean scores on the 12-item Short Form Health Survey (SF-12) and the EuroQoL (EQ-5D); anxiety as measured by mean scores on generalized anxiety disorder 7 (GAD-7); depression as measured by mean scores on the patient health questionnaire (PHQ-9); work productivity and activity assessment (WPAI:SHP) questionnaire; pain as measured by mean scores on the visual analogue scale (VAS), and the McGill pain questionnaire (MPQ). These outcomes will be measured via two online surveys prior to (T0) and post-intervention (T1). Questions on participants’ non-pharmacologic therapy preferences and experiences of participating in the trial will also be included, and measured at T0 and T1, respectively.  In addition to these self-reported questionnaires conducted via online surveys, objective measures will also be carried out by the research team at ECU Holistic Health Research Clinic, which is in the university’s Sport Centre where the Tai Chi/Qigong training program take place. These measures include flexibility as measured by the finger to floor distance (FFD); obesity as measured by mean scores on body mass index (BMI); Vital signs (blood pressure, heart rate, respiratory rate, temperate, and oxygen saturation) as measured by a blood pressure monitor, tympanic, and pulse oximetry device. These outcomes will be measured prior to (T0) and post-intervention (T1). People diagnosed with pre-diabetes or diabetes, their HbA1C and fasting BGL will also be measured via test kits at T0 and T1. | |
| **Sample Size:** Based on previous Tai Chi/Qigong exercise intervention studies, n = 20 participants will be required per group (total n=40) for this study. | |

Element 1

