Descriptive statistics for continuous variables will initially be described by mean and standard deviation (SD) for normal data, and by median and interquartile range (IQR) for non-normal data. Categorical data will be summarised by frequencies and proportions. The primary and secondary outcomes will be assessed following intention-to-treat principles. Linear mixed modelling with unstructured covariance matrix will be conducted to assess changes in outcomes throughout the study. This model allows for the inclusion of missing data in an intention-to-treat analysis without imputations (e.g., last-observation-carried-forward). Post-hoc tests will be conducted on all pairwise comparisons. The analysis will be adjusted for potential confounding factors such as age, gender, education levels and any other potentially relevant variables where data are available. The corrected Akaike Information Criterion (AICc) will be used to assess model fit when covariates are added to the model. Normality assumptions will be assessed using the Shapiro-Wilk test. If required, non-linear transformations such as the square root and log-transformations, will be applied to normalise the data. Statistical significance will be set at an alpha level of 0.05. False discovery rate (FDR). Corrections will be applied to all analysed outcomes to account for multiple comparisons. Effects sizes, defined by partial eta squared, will be reported and interpreted, with 0.01, 0.06 and 0.014, respectively, identified as small, medium and large effects (43). All analyses will be conducted using R version 4.1.

The qualitative data collected via open-ended questions across the two online surveys will be used to help explain or elaborate on the quantitative data. Qualitative data will be analysed using template thematic analysis. Template thematic analysis uses ‘a priori’ code frames to analyse and report on the data. The initial skeleton code frame is often formulated from the questions asked of participants and then built upon during analysis in an iterative process.

Element 2

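### The partial eta squared cut-offs are out of order: the large-effect threshold (0.014) is below the medium one (0.06), so the labelling rule contradicts itself

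*Protocol*

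**What the plan says.** The statistical analysis text is in the protocol section on how the planned methods achieve the aim. It sets the effect-size measure: "Effects sizes, defined by partial eta squared, will be reported and interpreted". The same sentence then gives the grading, "with 0.01, 0.06 and 0.014, respectively, identified as small, medium and large effects", and cites reference 43. The cut-offs appear nowhere else in the protocol.

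The same paragraph sets the inferential framework. The model is described as follows: "Linear mixed modelling with unstructured covariance matrix will be conducted to assess changes in outcomes throughout the study". On covariates it says: "The analysis will be adjusted for potential confounding factors such as age, gender, education levels". The test level is given separately: "Statistical significance will be set at an alpha level of 0.05", with false discovery rate corrections for all analysed outcomes. The synopsis gives the size of the trial: "n = 20 participants will be required per group (total n=40) for this study".

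**The concern.** The sentence ties each figure to its label in order, so large means 0.014. That lies just above the small cut-off (0.01) and well below the medium one (0.06). A graded scale has to increase, and this one does not. Any value from 0.014 up to 0.06 counts as large yet falls short of medium, and any value of 0.06 or more satisfies both labels.

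What is at stake is the wording of the results. The rule covers the primary and secondary outcomes, and the protocol gives no other yardstick for the size of an effect: it states no minimal important difference and no target effect behind the sample size. In a trial of 40 people, a threshold of 0.014 is low enough for chance differences to reach it often. A report that followed the rule to the letter could call a clearly non-significant difference a large effect.

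**Working it through.** **Inputs from the protocol.** Cut-offs 0.01, 0.06 and 0.014; 20 participants per arm, 40 in total; two arms, two time points (T0 and T1); alpha 0.05.

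**Assumptions, not in the protocol.** The effect graded is a 1-df group (or group-by-time) contrast. With complete data and no covariates its denominator df is 40 − 2 = 38. The number of covariates and the dropout are not fixed, so 28 df serves as a low value. As a high value, 76 df treats all 80 observations as independent (80 − 4).

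**Step 1: order.** 0.01 < 0.014 < 0.06. The large cut-off falls between small and medium.

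**Step 2: can the three figures be reproduced?** For two equal groups with standardised difference d, eta² = d²/(d² + 4). The values d = 0.2, 0.5 and 0.8 are a convention that the protocol does not state.

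- d = 0.2: 0.04/4.04 = 0.0099, which matches 0.01.
- d = 0.5: 0.25/4.25 = 0.0588, which matches 0.06.
- d = 0.8: 0.64/4.64 = 0.138, which rounds to 0.14, not 0.014.

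The first two figures are reproduced. The third differs from the expected value by one decimal place.

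**Step 3: how often chance reaches each cut-off.** For a cut-off c, F = [c/(1 − c)] × df2, and with no true effect P(eta² ≥ c) = P(F(1, df2) ≥ that value). At 38 df:

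- c = 0.014: F = (0.014/0.986) × 38 = 0.54, probability 46.7%.
- c = 0.06: F = (0.06/0.94) × 38 = 2.43, probability 12.8%.
- c = 0.14: F = (0.14/0.86) × 38 = 6.19, probability 1.7%.

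A simulation of 200,000 null trials with 20 per arm gave 46.7%, 12.7% and 1.7%.

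**Step 4: sensitivity to the df.**

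| Denominator df | P(eta² ≥ 0.014) | P(eta² ≥ 0.14) |
| --- | --- | --- |
| 28 | 53.4% | 4.2% |
| 38 | 46.7% | 1.7% |
| 76 | 30.2% | 0.07% |

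**Step 5: sensitivity to the reading.** If each value takes the label of the highest cut-off it passes, large covers only 0.014 to 0.06. At 38 df the chance of that label with no true effect is 46.7% − 12.8% = 33.9%.

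**Step 6: relation to the significance test.** At 38 df, a two-sided p of 0.05 corresponds to eta² = 0.097. A value of 0.014 has p = 0.47 and an observed difference of about 0.23 SD, since √0.54 × √(2/20) = 0.23.

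**The case against.** The strongest case on the other side is that the error does little harm. The cut-offs drive only a descriptive word. Inference rests on the mixed model, the 0.05 level and the false discovery rate correction, none of which uses these thresholds, so a result with p = 0.47 stays non-significant whatever it is called. An analyst would probably notice that the scale is impossible and not apply it. This stands, and it is why the point is minor. It does not remove the contradiction: a rule set in advance should not depend on someone noticing that it is wrong.

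A reader might infer that about half of all null outcomes will be reported as large. The documents do not support that as a prediction. It requires the scale to be applied literally, as at or above 0.014, with about 38 df; the share changes with the df and with how values of 0.06 or more are labelled.

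A reader might also take 0.14 as the documented value. It is not. Reference 43 is not at hand, and the 0.2, 0.5 and 0.8 anchors come from outside the protocol. The fit of the first two figures makes a misplaced decimal the likely explanation, but the protocol alone proves only that large must exceed 0.06.

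Finally, one might go on to argue that partial eta squared is a poor main measure and that an adjusted mean difference with a confidence interval should replace it. That is a separate reporting preference. The protocol does not say that partial eta squared replaces the model estimates, and such choices are commonly left to the statistical analysis plan, which is not shown. It is not part of this point.

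**Conclusion.** The cut-offs are wrong as written. This follows from the sentence itself and needs no outside source. The size of the consequence is conditional: with a literal at-or-above reading, a 1-df contrast and about 38 df, 47% of outcomes with no true effect would be labelled large, against 1.7% if the cut-off were 0.14. The other df and the alternative reading change the 47% but leave it far above 1.7%.

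It would go too far to say that the error undermines the trial's inference. No estimate, p-value, multiplicity decision or sample size depends on it. This is a minor, easily corrected error in a stated threshold.

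**What to change.** Check the cut-offs against the protocol's reference 43 and, if it confirms the assumption, change 0.014 to 0.14. If the reference gives another value, use that, provided the three figures increase and the large cut-off exceeds 0.06. Make the correction before any results are interpreted, so that it cannot look like a threshold moved after the fact.

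The cost is one figure in one sentence. Data collection, the model, the multiplicity correction and the sample size are unchanged.

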**Recruitment**

**How will participants be identified and initially contacted including screening processes?**

The snowballing process and public advertisement can identify potential participants. People interested in participating in the study will be encouraged to contact the research team via email for an eligibility check.

**How will formal recruitment of potential participants be conducted?**

The study will involve providing participants with a 12-week Tai Chi/Qigong exercise.

Participants who fulfil our inclusion and exclusion criteria will be assigned with a unique identification number and provided with a Participant Information Letter outlining what will be involved in the trial and an online survey starting with a consent form. People who gave consent will complete the online survey after ticking a box under the online consent form.

Participants who completed the online survey will be invited to ECU sports centre where the 12-week Tai Chi/Qigong exercise take place, the researcher team will carry out the baseline physical assessments (e.g., FFD, BMI, BP, and SpO2).

Following the completion for the baseline measurements, the participants will be assigned to either a control or treatment group, with the assistance of a blinded statistician, via a randomised block design. This ensures the sample number in each group remain relatively similar through the recruitment process until the quota is reached.

Element 3

**Consent**

**Informed consent procedure (including justification for a Waiver of Consent, opt out consent or deception strategies)**

Participant consent form and Participant Information Letter are attached.

Element 4

**Collection, Use and Management of Data and Information**

**Project dates**

**03/01/2022—02/03/2032**

**Data collection method and location including who will be responsible for the data collection**

Participation in this research project is voluntary. If one does not wish to take part, they do not have to. If participant decided to take part and later changed their mind, they are free to withdraw from the project at any time. If they decide to withdraw from the project after the data has been analysed, we will not be able to remove the individual data as this cannot be identified.

If participant do decide to take part, they will be given the Participant Information letter and consent form to sign. They decision to take part, or to take part and later withdraw, will not affect they relationship with the research team and any staff within the School of Nursing and Midwifery at ECU.

By sign the consent form, they consent to the research team collecting and using personal information about the participant for the research project. Any information obtained in connection with this research project that can identify participant will remain confidential. When all data collected are returned to the research team and automatically de-identified. They information will only be used for the purpose of this research project and it will only be disclosed with their permission, except as required by law.

It is anticipated that the results of this research project will be published and/or presented in a variety of professional forums. In any publication and/or presentation, the information will be provided in such a way that participants cannot be identified, except where requested for specific reasons, and then they will be asked to provide written consent.

In accordance with relevant Australian and/or Western Australian privacy and other relevant laws, participants have the right to request access to the information about them that is collected and stored by the research team. They also have the right to request that any information that they disagree to be corrected. They are encouraged to inform the research team member named at the end of this letter if they would like to access their information.

All data collected will be kept in accordance with ECU’s Data Management Policy. Electronic data will be stored on a secure Microsoft SharePoint site provisioned by ECU’s IT Services and physical records will be stored as required in ECU’s Records Management Policy. The data will be retained for a period of seven years and destroyed, if appropriate at the end of the retention period. Data will be de-identified when stored and at the end of the retention period, the data will be destroyed, if appropriate under the State Records Act.

There are no foreseeable risks associated with participation in this research project.

We will advise participants of the outcomes via email communication. We also intend to publish our results in research journals and present them at research conferences locally, nationally, and internationally. Participants' name or any other identifying information will not be included in any of the publications or presentations.

This research project will not start until we sought the approval of Edith Cowan University’s Human Research Ethics Committee under the National Health and Medical Research Council’s National Statement on Ethical Conduct in Human Research 2007 (Updated 2018).

**Data Collection Dates (when undertaking any data collection)**

**01/03/2022 to 02/02/2032**

**Elements 5, 6, and 7**

**Communication of Research Findings or Results to Participants; Dissemination of Project Outputs and Outcomes; After the Project**

Final Report / Report to Funding Body

Peer Reviewed Publication

Lay person summary (e.g., Brochure / Report)

Public presentation

Media release

Summary provided to participants

Conference presentation

Debriefing of participants

Other

**Risk**

**Physical Risks**

Tai Chi/Qigong exercise is safe and there are no foreseeable risks associated with participation in this research project.

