**Benefit of exploring these research questions**

Several studies demonstrated that Tai Chi/Qigong has many health benefits, such as decreased heart rate, decreased blood pressure, lowered lipid levels, decreased levels of stress hormones, enhanced immune function, and improved physical wellbeing and psychological wellbeing. However, there is no consolidated conclusion for Tai Chi/Qigong and more studies in this field are required to provide updated evidence. Therefore, this study aims to address this knowledge gap.

We hypothesize that Quality of life (QoL) in Tai Chi/Qigong group is better than the control group (usual care). We hope that the results of our research can be used to inform our knowledge about how to better manage chronic diseases that many Australians are suffering.

There are no foreseeable risks associated with this research project.

**Outline the design of this research; its methods and details of the instruments to be used to collect the data, including psychometric properties if applicable.**

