**PICOs:**

**P:** Adults aged 18 years and older will be recruited for this trial

**I:** 12-week Tai Chi/Qigong exercise + usual care

**C:** Waiting list control with usual care (e.g., other exercise)

**O:**

The primary outcome is quality of life as measured by mean scores on the 12-item Short Form Health Survey (SF-12) and the EuroQoL (EQ-5D). This outcome will be obtained via two online surveys: at baseline (T0) and post intervention (T1).

The secondary outcomes will include anxiety as measured by mean scores on generalized anxiety disorder 7 (GAD-7); depression as measured by mean scores on the patient health questionnaire (PHQ-9); work productivity and activity assessment (WPAI:SHP); pain as measured by mean scores on the visual analogue scale (VAS) and the McGill pain questionnaire (MPQ). These outcomes will be measured via two online surveys at T0 and T1. Questions on participants’ non-pharmacologic therapy preferences and experiences of participating in the trial will also be included, and measured at T0 and T1, respectively. Flexibility as measured by the finger to floor distance (FFD); obesity as measured by mean scores on body mass index (BMI); blood pressure (BP), and oxygen saturation (SpO2) as measured by a pulse oximetry device will also be carried out by the researchers, and these outcomes will be measured before the intervention (T0) and post intervention (T1).

**S:** This is a single-blind (assessors blind to group allocation), double-armed, randomised controlled trial on the therapeutic effect of a 12-week Tai Chi/Qigong exercise for adults.

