**Key inclusion exclusion criteria**

Inclusion criteria consist of (1) adults aged 18 years and older, (2) diagnosed with one or more chronic disease (e.g., pain, diabetes, cancer), (3) having no physical and mental limitations prohibiting exercise, and (4) willing and able to consent for participation in the trial. People who are pregnant or with a serious health conditions that incapable of completing 12-week Tai Chi exercise will be ineligible to participate.

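### The protocol asserts that the exercise is safe with no foreseeable risks, but plans no adverse-event collection in either arm, so the trial will yield no harms count

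*Protocol*

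**What the plan says.** Under Physical Risks the protocol states that "Tai Chi/Qigong exercise is safe and there are no foreseeable risks associated with participation in this research project". The section on the benefit of the research questions says "There are no foreseeable risks associated with this research project". The data-collection section says "There are no foreseeable risks associated with participation in this research project", and Psychological Risks repeats that sentence.

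The eligibility criteria require participants to be "diagnosed with one or more chronic disease (e.g., pain, diabetes, cancer") and also "having no physical and mental limitations prohibiting exercise". They add: "People who are pregnant or with a serious health conditions that incapable of completing 12-week Tai Chi exercise will be ineligible to participate".

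The outcome lists are in the synopsis, the PICOs section and the section on how the methods achieve the aim. Between them they cover quality of life, anxiety, depression, work productivity, pain, therapy preferences and trial experiences, flexibility, BMI, blood pressure and oxygen saturation. The synopsis adds further vital signs and, for participants with pre-diabetes or diabetes, HbA1c and fasting glucose. For the physical measures, the PICOs section says "these outcomes will be measured before the intervention (T0) and post intervention (T1"); the questionnaires follow the same two time points. None of the lists includes an adverse event, and the statistical analysis paragraph mentions no harms summary.

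**The concern.** Safety is stated as a fact, and the trial collects nothing that could bear on it. The overarching aim is strong evidence of therapeutic efficacy for chronic disease management. A reader of such a trial needs benefit set beside harm, and here only benefit could be reported.

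A statistical analysis plan could not repair this. What is collected is fixed in the protocol, and events that were never asked about cannot be tabulated later.

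There is also a consequence for the efficacy analysis. Participants may withdraw at any time, and the protocol does not provide for recording the reason. The mixed model uses whatever data are available, without imputation. Someone who stopped because of an injury would appear only as a missing T1 value, with nothing to show that the dropout was related to harm.

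**Working it through.** The protocol gives no figure on harms, so there is none to reproduce. The check is mainly a reading of the text, followed by a short illustration of scale.

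**Reading**

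1. *What is asserted.* Four sections say that no risk is foreseeable, and one of them (Physical Risks) adds that the exercise is safe.
2. *What is collected.* The three outcome lists, the intervention and control descriptions, the recruitment, data-collection and risk sections and the statistical paragraph were read for any definition, collection, grading, reporting or analysis of adverse events. There is none.
3. *What might show harm anyway.* The T0 and T1 scores for pain, anxiety, depression, quality of life and vital signs could show worsening that persists to T1. Open-ended answers could mention an event, but they are to be analysed thematically. None of these gives a count of events by arm, and a fall, an injury or a flare that resolved before T1 could leave no trace.
4. *Exposure.* Participants are expected at two of three weekly 45-minute sessions for 12 weeks. That is 2 × 12 = 24 sessions each, and 24 × 20 = 480 person-sessions in the Tai Chi arm at expected attendance.

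**Illustration of scale**

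Input from the protocol: n = 20 per arm (synopsis, Sample Size). Inputs assumed: true event rates p of 1%, 2%, 5% and 10%. The protocol gives no event rate.

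Chance of at least one event among 20 = 1 − (1 − p)^20:

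| Assumed rate p | Calculation | Result |
| --- | --- | --- |
| 1% | 1 − 0.99^20 | 18% |
| 2% | 1 − 0.98^20 | 33% |
| 5% | 1 − 0.95^20 | 64% |
| 10% | 1 − 0.90^20 | 88% |

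Exact upper bound on the event rate if events were recorded and none occurred among 20:

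- one-sided 95%: 1 − 0.05^(1/20) = 0.139, or 13.9%
- two-sided 95%: 1 − 0.025^(1/20) = 0.168, or 16.8%

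An event type with a true rate of 5% to 10% would therefore probably occur in the Tai Chi arm, and no planned item asks about it. Full recording with no events would still leave rates up to about 14% compatible with the data.

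**The case against.** **The eligibility criteria do not contradict the risk statement.** A reader might infer that the protocol excludes people because the exercise endangers them, and so contradicts itself. The text does not support that. The serious-condition exclusion is framed as being unable to complete the programme, which is a matter of feasibility. Pregnancy is excluded without a stated reason, and the criteria never mention risk. It is also consistent to exclude unfit people and then foresee no risk for those enrolled. This objection stands. What remains is a tension: a rule that some limitations prohibit exercise sits uneasily with an unqualified claim of safety in a chronically ill population.

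**Some harm would show.** A reader might infer that every harm would go unrecorded. That is too strong. Both arms complete pain, mood, quality-of-life and activity measures, and the experience questions could surface an event. This also stands in part. These measures reach only what persists to T1 or is volunteered, and they are planned as outcome scores or qualitative material, not as harms data.

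**Recording would not establish safety.** This is correct, as the 13.9% bound shows. The gain is a descriptive count and an honest risk statement, not a test of safety.

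**The participant information letter is not at hand.** It is described as attached, so what participants are told about risk cannot be judged here. That does not affect the protocol's own statements or its lack of adverse-event collection.

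**Conclusion.** The point holds as a gap in data collection joined to an unsupported assertion. Safety is declared in advance, no adverse-event collection is described for either arm, and the trial as written would produce no harms count. It does not invalidate the primary quality-of-life comparison, but it leaves the benefit-harm picture one-sided, and the sponsor should correct it.

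This conclusion rests on the protocol text alone. The 64% and 88% figures depend on assumed event rates and serve only to show scale. The 13.9% bound depends on 20 participants being observed and would be wider with dropout.

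**What to change.** 1. Remove the statements of safety and of no foreseeable risk from the benefit section, the data-collection section, Physical Risks and Psychological Risks. Say instead that harms will be recorded and that 20 per arm cannot establish safety, since zero events in 20 excludes only rates above 13.9% (one-sided 95%).
2. Add the same adverse-event item to the T1 survey in both arms, covering injury, fall, worsening symptoms and unplanned care.
3. Ask that item, with the reason for stopping, of anyone in either arm who withdraws. A T1 item alone would miss them.
4. Report counts by arm descriptively, outside the set of outcomes corrected for false discovery rate.
5. List any events noted in class separately and do not compare them between arms. The waiting-list arm has no equivalent contact, so pooling the two sources would tilt the counts towards Tai Chi.

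The cost is one survey item, a short withdrawal question, revised wording for the ethics committee and one descriptive table. The downsides are a little more participant and staff time and reliance on recall over 12 weeks.
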